### Procedure

A telephone interview will take place before enrollment, in which oral study information will be given and interested persons are screened for self-reportable inclusion and exclusion criteria. If eligibility is given, interested persons will be invited for the first of the 2 web-based study visits that are conducted online by trained clinicians (Master of Science psychologists). At the first web-based study visit (T0), written information about the study will be given and the self-reportable inclusion and exclusion criteria will be queried. After providing their informed consent, participants will take part in a video-based Structured Clinical Interview for DSM-5 disorders (SCID-5) [26] to verify the indication for psychotherapy and check for exclusion criteria. If participants fulfill the eligibility criteria, the baseline assessment (T0) as well as the subsequent randomization will take place. At the end of T0, participants of both groups will receive TAU in form of an information brochure about psychotherapy. Participants will be invited to voluntarily study the brochure until the second web-based study visit (T1) 2 weeks later. At the second web-based study visit (T1), the intervention group will participate in the video-based OIC. Subsequently, all participants will take part in the postassessment and an interview for assessing the capacity to consent and adverse events. Upon request, participants will receive their individual results report of the SCID-5 within 1 week after T1. Two weeks (T2) and 3 months (T3) after T1, participants will be invited to complete 2 web-based follow-up questionnaires. A detailed summary of all the instruments is provided in Table 1.

**Table 1 table1:** Schedule of enrollment, intervention, and assessment according to Standard Protocol Items: Recommendations for Interventional Trials (SPIRIT).

						Study period								
				Screening		Enrollment		Intervention		Postallocation				
				
Time point				–1		T0				T1		T2		T3

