**Modulators**														
	Psychopathology (suspected diagnosis; SCID-5^g^ interview)					✓								
	State anxiety (STADI^h^ subscale)									✓				
	Prior knowledge about psychotherapy (FPTM^i^ subscale)					✓								
	Prior psychotherapeutic experience (G-EEE^j^ subscale)					✓								
	Satisfaction with therapeutic relationship (HAQ^k^ subscale)					✓								
	Time spent with the information brochure (single item)					✓				✓				
	Sociodemographic characteristics (single item)					✓								
	Intake of mental health medication (SCID-5 interview)					✓								

^a^TEX-Q: Treatment Expectation Questionnaire.

^b^MacCAT-T interview: MacArthur Competence Assessment Tool for Treatment.

^c^DCS: Decisional Conflict Scale.

^d^ACMTQ: Autonomous Motivation for Therapy Scale.

^e^CSQ-8: 8-item Client Satisfaction Questionnaire.

^f^At follow-up (T2 and T3), (serious) adverse events will be assessed by self-report instead of an interview.

^g^SCID-5: Structured Clinical Interview for Diagnostic and Statistical Manual of Mental Disorders-fifth edition.

^h^STADI: State Trait Anxiety Inventory.

^i^FPTM: Questionnaire on Psychotherapy Motivation.

^j^G-EEE: Generic Rating for Treatment Pre-Experiences, Treatment Expectations, and Treatment Effects.

^k^HAQ: Helping Alliance Questionnaire.

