### Statistical Analyses

Linear mixed modeling for repeated measures will be conducted for the hypothesis referring to the primary outcome. Following the intention-to-treat approach, all randomized participants will be included in the analysis to avoid attrition bias. The model will contain one between-subject factor treatment (OIC + TAU vs TAU) and one within-subject factor time (T0, T1, and T2). Before linear mixed modeling, additional variables (eg, respective baseline scores, type of prior experiences with psychotherapy, prior knowledge about psychotherapy, satisfaction with the therapeutic relationship, state anxiety, the time of occupation with the information brochure) will be checked for significant associations with the respective outcomes to identify potential covariates. If there are additional covariates, they will be included in the linear mixed model. Group differences will be checked using Tukey posthoc tests. In case of imbalanced group sizes, Bonferroni-corrected posthoc tests will be carried out instead.

The analytical strategy of fitting linear mixed models will also be applied to all analyses, including secondary outcomes. Three exceptions for the described analytical strategy will be analyses including the secondary outcomes of capacity to consent, satisfaction with received information, and (serious) adverse events, for which group differences at postassessment will be examined by an independent sample two-sided *t* test, a Welch *t* test, or a Mann-Whitney *U* test. Intergroup differences at baseline will be detected using independent sample two-sided *t* tests, Welch *t* tests, or Mann-Whitney *U* tests (for continuous variables) and Pearson chi-square tests (for categorical variables). Partial eta squared will be reported for estimating the proportion of explained variance, with *η^2^*=0.01 indicating small, *η^2^*=0.06 indicating moderate, and *η^2^*=0.14 indicating large effects [40]. Cohen *d* will be determined as a measure of effect size for pairwise comparisons (standardized mean differences) by dividing the mean score difference between the groups to be compared by the pooled standard deviation. According to Cohen [40], values of *d*=0.2, *d*=0.5, and *d*=0.8 are considered to indicate small, medium, and large effect sizes, respectively.

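### The covariate rule can put state anxiety, measured only at T1 after OIC, into the primary and most secondary models, which can bias the treatment main effect and the post hoc arm differences in either direction

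*Protocol article*

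**What the plan says.** Protocol article, Statistical Analyses. For the primary outcome: "The model will contain one between-subject factor treatment (OIC + TAU vs TAU) and one within-subject factor time (T0, T1, and T2". Before fitting, a list of variables is screened; its last two items and the rule read "state anxiety, the time of occupation with the information brochure) will be checked for significant associations with the respective outcomes to identify potential covariates". The consequence of passing is stated without condition: "If there are additional covariates, they will be included in the linear mixed model". The same strategy is applied to the secondary outcomes, except capacity to consent, satisfaction with information and (serious) adverse events. No sentence restricts candidates to values taken before randomization, and none says whether a covariate enters as a main effect or by time.

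Protocol article, Table 1, Modulators. The row "State anxiety (STADI^h^ subscale)" has a single tick, under T1. The row "Time spent with the information brochure (single item)" has ticks under T0 and T1.

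Protocol article, Procedure. Randomization follows the baseline assessment at T0, and both groups receive the brochure at the end of T0. Then: "At the second web-based study visit (T1), the intervention group will participate in the video-based OIC". The next sentence is: "Subsequently, all participants will take part in the postassessment and an interview for assessing the capacity to consent and adverse events".

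**The concern.** A covariate in a randomized comparison should be something treatment cannot have changed. State anxiety has no T0 value, so if it passes the screen the model must use one recorded after allocation and, on the described visit order, after OIC. An effect of OIC on it is plausible: the consultation discusses negative effects and coping, anxiety about side effects is a secondary outcome, and feeling frightened is a predefined potential adverse event.

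The screen makes this worse, because the more strongly T1 anxiety is associated with treatment expectations, the more surely it is entered. The adjusted comparison then no longer estimates the total effect of offering OIC. The quantities exposed are ones the plan uses: the sample size section refers to main effects as well as the interaction, and the analysis section tests group differences post hoc.

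**Working it through.** **The plan's own figure.** Inputs from the Sample Size section: f = 0.125, two-sided α = .05, 80% power, N = 106. Assumed, because not stated: three time points, correlation 0.5 between them, sphericity. For the within-between interaction, λ = f²·N·m/(1 − ρ) = 0.015625 × 106 × 3 / 0.5 = 9.94. This gives power 0.807 at N = 106 and 0.799 at N = 104, so 106 reproduces. The covariate problem does not touch this calculation; f serves only as a yardstick for the bias.

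**Would the screen let the variable in?** With 122 participants, a variable correlated r with the outcome passes at .05 with a probability found from z = atanh(r)·√119. For r = 0.3, z = 0.3095 × 10.909 = 3.38, so the probability is about 0.92. For r = 0.2 it is about 0.60.

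**What adjustment does.** In a linear model, adjusted arm difference = unadjusted difference − (slope of outcome on anxiety) × (arm difference in anxiety). The document gives neither factor, so both are assumed:

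- OIC lowers anxiety by 0.3 SD, slope −0.3, total effect d = 2f = 0.25: the change is 0.3 × 0.3 = 0.09. The adjusted difference is 0.25 − 0.09 = 0.16, and 0.09/0.25 = 36% is lost.
- OIC raises anxiety by 0.3 SD, same slope: 0.25 + 0.09 = 0.34, an inflation of the same size.
- Shifts of 0.1 to 0.5 SD with slopes of 0.2 to 0.5 in absolute value: 0.02 to 0.25 SD, or 8% to 100% of 0.25.
- No shift in anxiety: no bias on average.

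The percentage depends on how f is read. If f is the interaction effect, with no arm gap at T0 and an equal gap δ at T1 and T2, then f = δ/√18 and δ = 0.125 × 4.243 = 0.53 SD. The same 0.09 is then 0.09/0.53 = 17%.

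**Which contrast is affected.** The first scenario was simulated (3,000 trials, 61 per arm, complete data, anxiety related to the outcome at T1 and T2 but not at T0):

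| Model | T1 arm difference | T0 arm difference | T1−T0 treatment-by-time contrast |
|---|---|---|---|
| No anxiety term | 0.256 | about 0 (0.256 − 0.254) | 0.254 |
| Anxiety as main effect only | 0.197 | −0.057 | 0.254 |
| Anxiety by time | 0.168 | – | 0.166 |

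The arithmetic agrees. A single slope averages to (0 + 0.3 + 0.3)/3 = 0.2, so every time point shifts by 0.2 × 0.3 = 0.06. The T1 difference drops, a false T0 difference appears, and the change between them is untouched. With a slope for each time, T1 shifts by 0.09 and T0 by nothing, so the contrast loses (0.254 − 0.166)/0.254 = 35%.

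**Brochure time.** The brochure is given at the end of T0 and read until T1, so the reading falls mainly before OIC. It still follows randomization, in participants who are not fully blinded.

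**The case against.** The best defence is that the hypothesis in the Introduction concerns a greater change from T0 to T2, which is the treatment-by-time contrast, and a time-constant covariate leaves that contrast unchanged in complete data. This stands. A reader might infer that the primary hypothesis test is necessarily biased; the document does not support that. Nor does it exclude a covariate-by-time term, and the main effect and post hoc differences are exposed either way.

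Other stronger readings also fail:

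- *Adjustment always shrinks the effect.* The Introduction warns that disclosing risks may do harm, so a rise in anxiety, and hence inflation, is as open as a fall.
- *State anxiety is an established mediator.* The article lists it as a modulator, separate from anxiety about side effects, and does not say that OIC targets it. The bias needs only that OIC shifts it and that it is associated with the outcome.
- *Brochure time is equally a consequence of OIC.* It is also ticked at T0, both arms get the same brochure, and the document does not say when participants learn their allocation.
- *Participants lost before T1 drop out of the model.* The plan provides multiple imputation when more than 2% of data is missing, which 15% anticipated dropout makes likely to apply.
- *The screen invites steering.* It tests association with the outcome, and the analyst is blinded to allocation.

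Table 1 does not place the anxiety scale within the T1 visit, but the Procedure describes no questionnaire there before OIC. Even a pre-OIC value would follow randomization. It can also be said that the list is only illustrative and that a separate analysis plan may settle the set. But state anxiety is named, and inclusion after passing is stated as a rule, so this is an instruction rather than an omission.

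**Conclusion.** The point holds for state anxiety. Followed as written, the rule can condition the primary model and most secondary models on a variable measured only after OIC. The treatment main effect and post hoc arm differences can then be biased in either direction; the treatment-by-time contrast is at risk only if the covariate enters by time or the data are incomplete. The size is unknown. The 0.09 SD illustration rests on an assumed 0.3 SD shift and slope of 0.3, and its share of the planned effect (36% of 0.25) on taking d as 2f. Brochure time is a lesser instance: not a safe covariate, but not shown to be affected by OIC.

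**What to change.** In Statistical Analyses, replace the significance screen with a covariate set fixed in advance and limited to variables measured before randomization, including the stratification factor (type of prior psychotherapy experience). State how each covariate enters the model. Remove T1 state anxiety and post-randomization brochure time from the covariate list for all outcomes, and use them only in mediation or process analyses labelled exploratory. The cost is a change of wording before the analysis; data collection, schedule and sample size (106, or 122 with the dropout allowance) stay as they are.

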As recently recommended by Papaioannou et al [39], (expected) adverse events and (expected) serious adverse events of OIC and of study participation per se will be assessed at postassessment by using a short interview. In addition to open questions about individual adverse events, 3 a priori developed items about potential adverse events (feeling confused, feeling frightened about potential negative effects of psychotherapy, experiencing doubts about the decision to start psychotherapy) and serious adverse events (suicidal ideation, self-harm, hospitalization) will be assessed. Each event will be rated by the interviewer according to severity (5-point Likert scale) and its potential causal relationship to the study participation (5-point Likert scale). For follow-up assessments (T2 and T3), a self-report will be used instead of an interview.

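### Adverse events are compared between arms only at T1, the visit at which OIC is given; the T2 and T3 reports have no stated arm comparison

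*Protocol article*

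**What the plan says.** The Statistical Analyses section applies a linear mixed model with time points T0, T1 and T2 to the primary outcome and extends it to the secondary outcomes, apart from three. It introduces them so: "Three exceptions for the described analytical strategy will be analyses including the secondary outcomes of capacity to consent". The full list and its time point read "capacity to consent, satisfaction with received information, and (serious) adverse events, for which group differences at postassessment will be examined". The tests named are an independent-sample t test, a Welch t test or a Mann-Whitney U test.

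The Procedure section fixes the order of events at T1: "At the second web-based study visit (T1), the intervention group will participate in the video-based OIC". It continues: "Subsequently, all participants will take part in the postassessment and an interview for assessing the capacity to consent and adverse events". On follow-up it says: "Two weeks (T2) and 3 months (T3) after T1, participants will be invited to complete 2 web-based follow-up questionnaires".

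Adverse and serious adverse events are not confined to T1. Table 1 marks them at T1, T2 and T3, and Secondary Outcome Measures explains the change of mode: "For follow-up assessments (T2 and T3), a self-report will be used instead of an interview". The same section predefines the serious items: "serious adverse events (suicidal ideation, self-harm, hospitalization) will be assessed". It also predefines three non-serious items (confusion, fear of negative effects of therapy, doubts about starting it). The interviewer rates each event for severity and for causal relation, both on 5-point scales.

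**The concern.** Three outcomes share one rule. Two of them, capacity to consent and satisfaction with information, are measured only at T1, so a single comparison at T1 suits them. Adverse events are the only one of the three measured again later, and the rule leaves those later measurements without an arm comparison.

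This matters because the Introduction presents disclosure of risk as possibly harmful in itself, and the Discussion suggests that, if OIC proves effective, patients could be told of risks without breaching nonmaleficence. A non-significant result from the visit at which OIC was given could be taken as support for that on delayed and serious harms, which it cannot address.

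**Working it through.** The plan gives no adverse-event rate and no figure for this comparison, so there is none to reproduce. The main check sets schedule against analysis.

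**Schedule against analysis rule**

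| Outcome | Measured (Table 1) | Arm comparison stated |
|---|---|---|
| Capacity to consent | T1 | T1 |
| Satisfaction with information | T1 | T1 |
| Adverse and serious adverse events | T1 (interview), T2 and T3 (self-report) | T1 only |

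**Time after OIC covered**

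- Up to OIC, both arms have had the same brochure for the 2 weeks from T0 to T1.
- The T1 interview follows OIC within the same visit. The article does not give the interval.
- T2 is 2 weeks and T3 is 3 months after T1. All follow-up beyond the T1 visit is therefore in reports with no stated comparison.
- Putting adverse events back under the mixed model would not close the gap, because its time factor ends at T2.

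**Which events T1 can show**

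- Confusion, fear and doubt can be present straight after an information session, and the interview also asks about expected events. T1 is informative for these.
- Self-harm or hospitalization resulting from OIC can hardly occur between OIC and an interview in the same visit, and suicidal ideation arising later cannot be recorded there.

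**Illustration of direction, with assumed rates**

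Inputs: n = 61 per arm (Sample Size section), two-sided α = .05 (end of Statistical Analyses). The cumulative risks of 10% and 30%, and the share s of events visible by T1, are assumptions. With p1 = 0.10s, p2 = 0.30s, d = p2 − p1 and p̄ their mean,

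power = Φ{[d − 1.96·√(2p̄(1−p̄)/n)] / √([p1(1−p1) + p2(1−p2)]/n)}.

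- s = 1 (10% vs 30%): (0.200 − 1.96 × 0.0724)/0.0701 = 0.83, power about 80%.
- s = 0.5 (5% vs 15%): (0.100 − 1.96 × 0.0543)/0.0536 = −0.12, power about 45%.
- s = 0.33 (3.3% vs 9.9%): (0.066 − 1.96 × 0.0450)/0.0446 = −0.50, power about 31%.

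With assumed risks of 5% and 20%, the same three shares give about 71%, 40% and 28%.

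**What an interval adds for event occurrence**

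With no events in n participants, the exact two-sided 95% upper limit is 1 − 0.025^(1/n). For n = 61 this is 1 − 0.9413 = 5.9%. For n = 53 (half of the 106 in the sample size calculation) it is 6.7%. A p value from a t or rank test does not show this limit. It would apply at any time point, so it illustrates the reporting format and does not measure the cost of stopping at T1.

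**The case against.** The strongest reply is that T1 is the best measurement of harm in the trial. It is the only one made by interview, and the Blinding section says those assessors do not know the allocation. T2 and T3 are self-reports from participants who cannot be fully blinded. The predefined non-serious events are immediate reactions, for which T1 is the natural time point. The hypotheses include none on adverse events. They approach harm from disclosure through side-effect expectations and decisional conflict, which the mixed model compares between arms through T2. A rank test also suits 5-point severity ratings. Finally, an article condenses a fuller plan, and tabulation of harms is often left to that plan.

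Most of this stands, and it limits the point. A reader might infer that follow-up harms will never be examined by arm, that a null result at T1 is uninformative, or that the named tests are simply wrong. The documents support none of these. The article does not exclude a T2 or T3 summary elsewhere; T1 is informative for immediate and expected events; and the article nowhere says that events are rare or recorded only as present or absent.

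The reply does not account for the follow-up reports. The article is not silent: it names adverse events as an exception and fixes their time point. Side-effect expectations and decisional conflict do not stand in for self-harm or hospitalization, and their comparison ends at T2. Better measurement at T1 is a reason to keep that comparison, not to leave later reports without one.

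**Conclusion.** The point holds in a limited form. Under the analysis that the article states, arms are compared on adverse and serious adverse events only in the visit at which OIC is given, although both are collected for 3 months afterwards. That comparison is useful for immediate reactions and expected events, and carries almost no information on delayed events or serious events resulting from OIC.

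The loss cannot be sized from the document, which gives no event rates. The power figures rest on assumed risks and show direction only. The judgement on serious events assumes that they take longer to arise than the gap between OIC and the interview. The choice of test for event occurrence is secondary. The primary outcome is unaffected; what is at stake is what the trial can say about harm.

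**What to change.** Keep the blinded T1 interview comparison, with rank tests for the severity ratings. Add a comparison of the proportion of participants with at least one adverse event and, separately, at least one serious adverse event: at T2, at T3, and cumulatively from OIC to T3. Give risk differences with exact or score 95% confidence intervals.

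Show the T2 and T3 self-reports separately from the T1 interview as well as combined, and state the change of mode and of blinding beside the combined figure. State also how participants with a missing T2 or T3 report are counted in the cumulative proportion.

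The cost is a few sentences of analysis text; no new assessment is needed. The drawback is that reporting bias can enter the follow-up and cumulative comparisons, which is why the T1 result should stay visible on its own.

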	**Secondary end points**													
		Capacity to consent (MacCat-T^b^ interview)							✓					
		Decisional conflict (DCS^c^)			✓				✓		✓			
		Side effects of psychotherapy: occurrence expectations, anxiety, and expected coping (3 constructed items)			✓				✓		✓			
		Autonomous treatment motivation (ACMTQ^d^ subscale)			✓				✓		✓			
		Adherence intention (3 constructed items)			✓				✓		✓			
		Interest in and knowledge about psychotherapy in general (2 constructed items)			✓				✓		✓			
		Knowledge about what is meant by psychotherapy, its effectiveness, key mechanisms, side effects, legal and organizational aspects (5 constructed items)			✓				✓		✓			
		Information-seeking behavior toward finding a treatment (3 constructed items)									✓		✓	
		Utilization of treatment services (6 constructed items)									✓		✓	
		Satisfaction with received information (CSQ-8^e^)							✓					
		(Expected) adverse events (interview)							✓		✓^f^		✓^f^	
		(Expected) serious adverse events (interview)							✓		✓^f^		✓^f^	

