### Secondary Outcome Measures

The capacity to consent to treatment will be assessed by an adapted German version of the semistructured interview MacArthur Competence Assessment Tool for Treatment (MacCAT-T) [32,33]. Subscale scores, ranging from 0 to 6 (understanding), 0 to 8 (reasoning), 0 to 4 (appreciation), and 0 to 2 (choice), as well as the total sum score, ranging from 0 to 20, will be used for all required analyses. Higher scores indicate higher capacity to consent. Since the MacCAT-T provides a wide range of applications (eg, for dementia), the exact wordings of the questions have been rephrased and adapted to the psychotherapeutic context. Given that risks of psychotherapy may be diverse and multifaceted, it has been deemed sufficient if participants can name 1 risk of psychotherapy instead of 2, as demanded in the original form of the MacCAT-T. Thus, the maximum score of 2 in the item “understanding of benefits and risks” (subscale understanding) can be achieved, even if just 1 risk of psychotherapy can be expressed adequately. The ranges of all subscale scores as well as the range of the total sum score do not change due to this modification.

Decisional conflict will be assessed using the Decisional Conflict Scale [34,35]. The Decisional Conflict Scale consists of 16 items, which are divided into 5 distinct domains: uncertainty, informed, values clarity, support, and effective decision. All items are presented on a 5-point Likert scale, ranging from “not correct at all” to “fully correct.” A total score and 5 subscale scores, each ranging from 0 to 100, will be used for analyses, with higher scores indicating higher decisional conflict. The perceived support in decision-making for or against the utilization of psychotherapy is assessed by 1 self-developed item that is presented on an 11-point Likert scale, ranging from 0 to 10, with higher scores indicating greater perceived support.

Three additional items were developed in advance to assess participants’ (1) expectations about experiencing side effects of psychotherapy, (2) anxiety about experiencing side effects, and (3) expectations about coping with side effects. The corresponding items will be presented on an 11-point Likert scale, ranging from 0 to 10, with higher scores indicating higher expectation about occurring side effects, anxiety about side effects, or respective coping expectations.

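### Capacity to consent and satisfaction are compared at T1 without covariates, although prior knowledge and the randomisation stratum are known at T0; the test is valid but may lose precision

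*Protocol article*

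**What the plan says.** The general strategy in Statistical Analyses is a linear mixed model, preceded by a check of candidate covariates. The candidates include type of prior experience with psychotherapy and "prior knowledge about psychotherapy, satisfaction with the therapeutic relationship, state anxiety". The consequence is tied to that model: "If there are additional covariates, they will be included in the linear mixed model".

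The same section then makes exceptions, opening with "Three exceptions for the described analytical strategy will be analyses including the secondary outcomes of capacity to consent". The full list and its test read "capacity to consent, satisfaction with received information, and (serious) adverse events, for which group differences at postassessment will be examined by an independent sample" t test, with a Welch t or Mann-Whitney test as the alternatives. No covariate or stratum term is mentioned.

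Table 1 shows why a repeated-measures model is not used. The row "Capacity to consent (MacCat-T^b^ interview" has a single tick, at postassessment, and so has the CSQ-8. The same table lists "Prior knowledge about psychotherapy (FPTM^i^ subscale" among the modulators with one tick, read as T0. It also lists "Knowledge about what is meant by psychotherapy, its effectiveness, key mechanisms, side effects, legal and organizational aspects (5 constructed items" with three ticks, read as T0, T1 and T2.

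The Randomization section stratifies on prior psychotherapy experience (none, positive, negative). Secondary Outcome Measures gives the MacCAT-T total a range of 0 to 20 ("Higher scores indicate higher capacity to consent") and the CSQ-8 a range of 8 to 32.

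**The concern.** Neither score has a baseline of its own, so neither can gain precision from one. The trial does hold two pieces of pre-randomisation information that could predict them: what the participant already knew about psychotherapy, and the type of earlier experience with it. The article regards both as worth checking for every outcome that goes into a mixed model, but uses neither for these two.

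A link with the MacCAT-T is plausible because one of its subscales scores understanding. If the link exists, the unadjusted comparison leaves explainable variation in the error term. The cost falls on a measure that carries particular weight here. Participants cannot be fully blinded, and the questionnaires are self-report. Apart from adverse events, the MacCAT-T is the only outcome obtained by a blinded interviewer.

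**Working it through.** **The plan's own figure.** The article states 106 participants for 80% power at f = 0.125 with two-sided α = .05. For a group-by-time interaction with 2 groups and m = 3 time points, λ = f²·N·m/(1 − ρ), with (m − 1) and (N − 2)(m − 1) degrees of freedom. Taking ρ = 0.5 and sphericity (neither is stated), λ = 0.015625 × 106 × 3 / 0.5 = 9.94 on 2 and 208 df. Power is 80.7% and the required N is 106, so the figure reproduces. It concerns the primary outcome only; the article gives no power for capacity or satisfaction.

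**Inputs for the check.**
- Participants per arm: 106/2 = 53. The best case is 61, with nobody lost by T1.
- α = .05, two-sided (article).
- Standardised difference d: not in the article for these outcomes. Assumed 0.5, with 0.25 as a smaller alternative.
- Correlation r between the T0 covariate and the T1 score: not in the article. Assumed range 0.1 to 0.6.

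**Formula.** Adjusting for a baseline covariate multiplies the residual SD by √(1 − r²). The noncentrality is d/√(1 − r²) × √(n/2), on 2n − 2 df unadjusted and 2n − 3 df with one covariate. At n = 53 and d = 0.5:
- unadjusted: 0.5 × √26.5 = 2.574 on 104 df;
- r = 0.3: 2.574/√0.91 = 2.698 on 103 df;
- r = 0.5: 2.574/√0.75 = 2.972 on 103 df.

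**Power (%).**

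| n per arm, d | unadjusted | r = 0.1 | 0.2 | 0.3 | 0.4 | 0.5 | 0.6 |
|---|---|---|---|---|---|---|---|
| 53, 0.5 | 72.2 | 72.7 | 74.0 | 76.2 | 79.4 | 83.8 | 89.0 |
| 61, 0.5 | 78.2 | 78.6 | 79.8 | 81.9 | 84.8 | 88.5 | 92.8 |
| 53, 0.25 | 24.7 | 24.9 | 25.6 | 26.7 | 28.5 | 31.3 | 35.7 |

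In the first row the gain is 0.5 points at r = 0.1, 1.8 at 0.2, 4.0 at 0.3, 7.2 at 0.4, 11.6 at 0.5 and 16.8 at 0.6. Put another way, the difference detectable with 80% power at 53 per arm falls from d = 0.550 unadjusted to 0.525 (r = 0.3) or 0.476 (r = 0.5).

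With the stratum in the model as well, r is read as the multiple correlation. The three-level stratum costs two further df (101 instead of 103), which is negligible at this size.

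**The choice among three tests.** Null trials were simulated (20,000 runs, 53 per arm), once with normal scores and once with scores capped at 20. If the test is chosen by checks of normality and variance, the type I error is 5.1% and 5.0%. If the smallest of the three p-values is always taken, it is 5.9% and 6.1%.

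**The case against.** The strongest reply is that nothing here is wrong. Both scores are measured once, so the exception to the repeated-measures strategy is reasonable, and an unadjusted two-group comparison is valid after randomisation. That stands. Leaving out a prognostic stratum makes such a test conservative if anything. Both outcomes are secondary, no hypothesis in the Introduction names them, and no power target covers them.

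The size of the gain is also open to challenge. Understanding supplies only 6 of the 20 MacCAT-T points; reasoning, appreciation and choice supply the other 14. One named risk is enough for full marks on the benefits-and-risks item. Prior knowledge may therefore predict the total only weakly. For the CSQ-8 there is less reason still to expect that prior knowledge predicts satisfaction with the information received. T1 is the first visit after randomisation, two weeks on, so attrition may be light and unadjusted power nearer the 78% seen at 61 per arm. All of this limits the gain. None of it is a reason to set aside baseline data already collected.

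A reader might infer two stronger points that the article does not support:
- **That capacity is the only outcome measuring the validity of consent.** The Introduction lists five components of truthful consent, of which capacity is one and understanding another. The knowledge items, the Decisional Conflict Scale and autonomous motivation bear on the others.
- **That naming three tests materially inflates type I error.** The simulation shows about 5% when assumption checks guide the choice and about 6% in the worst case. The selection rule is also a detail that a condensed article may leave to an analysis plan not shown here.

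**Conclusion.** The point holds as a modest, nearly free improvement to a stated analysis. For the MacCAT-T and CSQ-8 totals the plan uses neither a T0 covariate nor the randomisation stratum, although it treats both as candidates elsewhere. The result would be unbiased but possibly less precise than it need be.

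At 53 per arm and d = 0.5, the gain in power is 4 points or less for r up to 0.3, and about 7 to 12 points for r of 0.4 to 0.5. Both d and r are assumptions. At d = 0.25 the gain at r = 0.3 is only 2 points (24.7% to 26.7%). The case is better for the MacCAT-T than for the CSQ-8.

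**What to change.** For the MacCAT-T total and for the CSQ-8 total, pre-state one linear model each. Include arm, the prior-experience stratum (three levels) and the T0 FPTM prior-knowledge score, and use heteroscedasticity-robust standard errors. Report the adjusted mean difference on the 0 to 20 or 8 to 32 scale with its 95% confidence interval. Keep a rank test as a sensitivity analysis.

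Name the FPTM subscale explicitly. The T0 knowledge items are the alternative, but they belong to a secondary outcome and the article describes no combined score for them. Fix the covariates in advance, without a significance screen. Adverse events are not part of this change.

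A model of this kind also yields an estimate and standard error that can be pooled if the planned multiple imputation is triggered, which a Mann-Whitney test does not directly give.

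The cost is a sentence or two of analysis text. No new data are needed, since the stratum and the FPTM score are already recorded at T0.
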